### Recruitment

#### Training of participants

Prior to the start of the clinical trial, the supervisor and the person in charge of each trial center should conduct training for the participants on the trial protocol in order to make the participants understand and be familiar with the nature, effects, efficacy, and safety of the trial drug (including relevant information on the preclinical studies of the drug), and also to grasp all the new information related to the drug that is found during the conduct of the clinical trial.

### Quality control

Both sponsors and participants should adopt standard operating procedures to ensure quality control and the implementation of the quality assurance system of the clinical trial. All observations and findings in clinical trials should be verified to ensure the data’s reliability and that all conclusions in clinical trials are derived from the original data. Quality control must be applied at every data processing stage to ensure that all data are reliable and correctly processed.

### Monitoring

The sponsor appoints a monitor to conduct regular on-site monitoring visits to the trial hospital to ensure that all elements of the study protocol are strictly adhered to and that the original data are checked to ensure consistency with the CRF form.

### Data management

The participant will complete the case report form and then checked and approved by the clinical supervisor before being delivered to the full-time data manager to set up a database. The data on the CRF form will be entered into the database independently in duplicate by two data entry personnel, reviewed manually, checked by the computer, and then blinded before the data are locked for statistical analysis.

### Intervention measures

#### Control group

The control group received placebo Tablet that were identical in appearance to the KYCT. Placebo Tablet, which weigh 0.3g per tablet, were manufactured by Beijing Qinuo Biotechnology Company Limited. Participants took 1.2g placebo (4 Tablet) twice daily with warm water 30 minutes after meals.

#### Intervention group

The intervention group received KYCT weighing 0.3g per tablet, manufactured by Beijing Qinuo Biotechnology Company Limited. Participants took 1.2g per dose (4 Tablet) twice daily, with warm water 30 minutes after meals.

During the trial, all participants received standard care, including (1) dietary control, including adopting a low-calorie diet, maintaining ideal body weight, avoiding high-purine foods, strictly abstaining from all kinds of alcohol, and drinking at least 2000 ml of water per day; (2) trigger avoidance, including quitting smoking, avoiding overeating, avoiding excessive fatigue and mental stress, and avoiding the use of drugs that severely affect uric acid excretion, such as some diuretics; (3) prevention and treatment of comorbidities, including hyperlipidemia, diabetes, hypertension, coronary heart disease, cerebrovascular disease, etc.

During the trial, all participants were provided with a uniform treatment medication for gout attacks: 60 mg of Etoricoxib Tablet (manufactured by Hangzhou MSD Pharmaceutical Co., Ltd., China, 60 mg/tablet, Batch No. J20180059), taken once daily, with a 7-day supply provided to patients at the time of enrollment.

The study medication was immediately discontinued if SUA levels were <180 umol/L during the visit.

### Result assessment

Evaluators assessed all relevant indicators at baseline, 4th, 8th, and 12th week. Details of the assessments are provided in **Table 1**.

**Table 1 T1:** Schedule for data collection, the process of the assessments per visit.

measures	Baseline	Intervention phase		
Time(weeks)	-2-0	4	8	12
Informed consent	**✓**			
Demographics and Past medical history	**✓**			
Physical examination	**✓**	**✓**	**✓**	**✓**
Laboratory Tests	**✓**	**✓**	**✓**	**✓**
Electrocardiogram	**✓**			**✓**
Acertainment of Inclusion and Exclusion Table	✓			
Distribution of the study medicine		✓	✓	
Drug recovery		✓	✓	✓
Routine follow-up measurement table		✓	✓	✓
Adverse events		✓	✓	✓
Endpoint events		✓	✓	✓
Medication adherence assessment		✓	✓	✓

#### Screening criteria

Urine pregnancy tests were performed in premenopausal female subjects and were evaluated before medication and at week 12 of medication.

#### Efficacy endpoints

##### Primary efficacy endpoint

The proportion of participants who maintained SUA levels <420 umol/L at week 12 (SUA levels were uniformly determined by uricase-peroxidase coupling assay, as described in Appendix 1).

##### Secondary efficacy endpoints

Proportions of participants maintaining sUA level <360 umol/L at week 12; percent change of sUA level from baseline to each visit; maximal percent change of sUA level from baseline to week 12; changes in anthropometric parameters (body weight, waist circumference, hip circumference, BMI), blood pressure, lipid profile, and fasting blood glucose level; number of gout flares reported; proportion of participants with gout flares cumulatively assessed at each visit.

##### Prespecified exploratory endpoint

The percentage of participants achieving a minimal clinically important difference (MCID) in serum uric acid (sUA) reduction (≥1.5 mg/dL from baseline) is noteworthy. This threshold is based on the following considerations:

Gout flare prevention: A reduction of ≥1.0 mg/dL is associated with a 50% decrease in flare risk (28).Renal protection: A reduction of ≥1.5 mg/dL is correlated with a diminished decline in estimated glomerular filtration rate (eGFR) in individuals with chronic kidney disease (29).

#### Safety endpoints

Vital signs (body temperature, respiratory rate, heart rate, blood pressure), liver function, renal function, complete blood count, and urinalysis indicators will be evaluated at baseline, weeks 4, 8, and 12 during the study period. A 12-lead electrocardiogram will be evaluated at baseline and week 12 during the study period.

All blood samples were collected after a 12-hour fast (refrain from eating or drinking) between 8:00 and 10:00 a.m. Blood samples will be collected at each participating center; all centers are tertiary hospitals with reliable laboratory facilities. All samples were processed promptly at the local tertiary hospital laboratories.

### Data analysis

The complete analysis set (FAS) and per protocol set (PPS) were used for efficacy evaluation analysis. The safety set (SS) was used for safety indicator analysis; since concomitant medications may affect efficacy and safety, the overall combination therapy was analyzed using the SS. General data was analyzed using the FAS and PPS. The last observation was carried forward for efficacy analysis for participants who withdrew prematurely. Dropouts with baseline data were included in efficacy analyses using the last observation carried forward. Excluded cases were not included in the efficacy statistical analysis, but those who received at least one treatment and had at least one safety record participated in the adverse reaction analysis.

To address potential confounding from lifestyle modifications, we will implement a three-pronged strategy to differentiate the specific effects of KYCT from those attributable to dietary control and health education. First, the double-blind placebo-controlled design ensures both groups receive identical lifestyle interventions, with KYCT administration being the sole therapeutic distinction between arms. Second, our primary analysis will employ analysis of covariance (ANCOVA) adjusting for key lifestyle covariates including physical activity levels (measured in MET-minutes/week) and daily purine intake (quantified through 24-hour dietary recalls). Third, sensitivity analyses will examine treatment effects in predefined adherent subgroups (≥80% protocol compliance for both medication intake and lifestyle recommendations) to assess outcome robustness against potential lifestyle adherence variations.

Furthermore, to address potential heterogeneity in treatment effects across subpopulations, three methodological safeguards have been incorporated: First, stratified randomization by baseline sUA tertiles (7.0-7.5, 7.6-8.5, >8.5 mg/dL) and sex ensures balanced subgroup distributions. Second, pre-specified Bayesian hierarchical models with regularizing priors [N(0,1)] will estimate subgroup effects while pooling information across multicenter clusters. Third, all subgroup comparisons will apply Benjamini-Hochberg FDR correction (<10%) within stratification categories, with results explicitly interpreted as exploratory hypotheses per CONSORT extension guidelines.

Statistical analysis was performed using SPSS 20.0 software. We presented the results as mean ± standard deviation for quantitative data that followed a normal distribution. We used an independent sample t-test to compare differences between the two groups and a paired sample t-test to compare differences within each group before and after the intervention. We presented the results as the median and interquartile range for quantitative data that followed a skewed distribution. We used the Mann-Whitney test to compare differences between the two groups and the Wilcoxon test to compare differences within each group before and after the intervention. We used Spearman correlation analysis to examine the correlation between variables. A significance level of P < 0.05 was considered statistically significant.

The proportion of participants attaining the MCID (≥1.2 mg/dL sUA reduction) will be compared between treatment arms using logistic regression, adjusted for baseline sUA levels and stratification factors (sex, baseline sUA tertiles). Results will be interpreted as hypothesis-generating, with 95% confidence intervals reported to quantify precision. Sensitivity analyses will assess MCID consistency across predefined subgroups (baseline sUA strata, renal function categories).

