### Inclusion criteria

(1) Age 18–70 years (at the time of obtaining informed consent), any gender; (2) Meet the diagnostic criteria for asymptomatic HUA; (3) Blood uric acid level > 8.0 mg/dL (480 μmol/L) at enrollment after 1 month or longer of low purine dietary control; (4) No history of acute gout attack before enrollment; (5) Normal electrocardiogram at enrollment; (6) Able to swallow Tablet; (7) Voluntarily participate, able to comply with regular follow-up and complete patient logs, and sign an informed consent form.

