### Handling of dropout cases

Subjects who withdraw prematurely from the trial or are lost to follow-up will be contacted to complete a final assessment. Every effort will be made to collect efficacy and safety data for these subjects. Reasons for premature withdrawal will be documented in the case report form and trial conclusion form.

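### Carrying the last observation forward lets a week-4 or week-8 value from someone who has left the trial count as success at week 12, which can favour KYCT

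*Protocol article*

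**What the plan says.** The primary endpoint (Primary efficacy endpoint) is "The proportion of participants who maintained SUA levels <420 umol/L at week 12". SUA can come from four occasions: "Evaluators assessed all relevant indicators at baseline, 4th, 8th, and 12th week" (Result assessment).

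The Data analysis section gives the missing-data rule twice. The first statement is "The last observation was carried forward for efficacy analysis for participants who withdrew prematurely". The second is "Dropouts with baseline data were included in efficacy analyses using the last observation carried forward". Neither excepts the primary endpoint. The other efficacy analyses named there are the per-protocol set and a sensitivity analysis in adherent subgroups. Neither varies what is assumed about missing week-12 values.

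Under Handling of dropout cases, the article adds: "Subjects who withdraw prematurely from the trial or are lost to follow-up will be contacted to complete a final assessment". It does not say when that assessment takes place or how its result enters the analysis.

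**The concern.** The endpoint is a claim about week 12. Carrying forward a week-4 value assumes that SUA stays on the same side of 420 for the remaining 8 weeks; carrying forward a week-8 value assumes it for 4 weeks. For a laboratory value expected to depend on the drug, in someone who has left, nothing in the article supports that assumption.

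The routes into the rule are ordinary ones: withdrawal for a serious adverse event or for poor compliance (Withdrawal criteria), loss to follow-up, and emergency unblinding, after which the participant is handled as a dropout (Random allocation and blinding).

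If KYCT lowers SUA while it is taken, more KYCT than placebo dropouts may leave with a last value below 420, even when the same number leave each arm. Those values then count as observed week-12 successes. The effect estimate and its test would rest partly on values that were never measured, and no stated analysis would show how much that matters.

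**Working it through.** **Inputs from the article.** Success rates 60% and 30%, two-sided alpha 0.05, power 0.80, dropout 15%, 53 per group raised to 63 (Sample size calculation). Entry SUA above 480 µmol/L (Inclusion criteria). SUA at weeks 4, 8 and 12 (Table 1).

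**Inputs that are assumptions.** The share of dropouts whose carried value is below 420, the share truly at target at week 12, and any imbalance in dropout. The article gives none of these.

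**The plan's own figure.** The dropout step reproduces: 53 / 0.85 = 62.4, so 63 per group and 126 in total. The 53 does not: the usual two-proportion formula gives 42 per group, or 49 with continuity correction. The stated size is on the large side. That is a separate matter and does not affect this point.

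**Participants affected.** 63 × 0.15 = 9.45, about 9 per arm; 126 × 0.15 = 18.9, about 19 in total.

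**Planned effect.** Let d be the dropout share, p the completer success rate and q the share of dropouts whose carried value succeeds. The scored rate is (1 − d)p + dq. Counting dropouts as failures sets q = 0.

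| Scenario, d = 15% in both arms | KYCT | Placebo | Difference |
|---|---|---|---|
| Dropouts counted as failures | 0.85 × 0.60 = 51.0% | 0.85 × 0.30 = 25.5% | 25.5 points |
| Carried, q = 60% / 30% | 51.0 + 9.0 = 60.0% | 25.5 + 4.5 = 30.0% | 30.0 points |
| Carried, q = 80% / 30% | 51.0 + 12.0 = 63.0% | 25.5 + 4.5 = 30.0% | 33.0 points |
| Carried, q = 30% / 15% (for example, half the dropouts have only a baseline value) | 51.0 + 4.5 = 55.5% | 25.5 + 2.25 = 27.75% | 27.75 points |

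The gap from failure counting is 4.5, 7.5 and 2.25 points in turn, so 4.5 is not a ceiling.

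**Null illustration.** Suppose 30% of completers succeed in both arms, 15% drop out of each arm, and no dropout is truly at target at week 12. The true rates are 0.85 × 0.30 = 25.5% in both arms, a difference of zero. If carried values succeed in 60% of KYCT and 30% of placebo dropouts, the scored rates are 25.5 + 9.0 = 34.5% and 25.5 + 4.5 = 30.0%. The 4.5-point difference is spurious. At 63 per arm, rejection at nominal two-sided 5% is 8.4%, by normal approximation and by exact enumeration of the chi-square test.

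**Power if dropouts count as failures** (exact chi-square, 63 per arm):
- No loss to failure counting, 60% v 30%: 0.940.
- 15% dropout in both arms, 51% v 25.5%: 0.855 (0.86).
- 20% in both arms, 0.80 × 60 = 48% v 0.80 × 30 = 24%: 0.816 (0.82).
- 20% on KYCT and 10% on placebo, 48% v 0.90 × 30 = 27%: about 0.70.

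**The case against.** The strongest reply is that the comparison does not demonstrate bias. Counting every dropout as a failure is also an assumption. In the main scenario, carrying forward simply returns the planned 60% and 30%. The plan itself expects 30% success on placebo, so some dropouts would be at target without active drug. This stands: the 4.5 points are bias only to the extent that dropouts are not at target at week 12.

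Second, the direction is not fixed. Entry requires "Blood uric acid level > 8.0 mg/dL (480 μmol/L) at enrollment after 1 month or longer of low purine dietary control", so a dropout with only a baseline value is carried as a failure, the same result as under failure counting. (Ineligibility criteria also lists participants without follow-up data, and excluded cases leave the efficacy analysis. That needs reconciling with keeping dropouts who have baseline data.) The assessment for which withdrawn participants "will be contacted to complete a final assessment" might yield an off-drug value that becomes the last observation. Both points stand. The second gives limited comfort, because nothing ties that assessment to week 12 or says how it is used.

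A reader might also infer that the drug-stopping rule produces automatic successes: "The study medication was immediately discontinued if SUA levels were <180 umol/L during the visit". The article does not support this. It stops the drug; it does not say that the participant leaves the trial, and Withdrawal criteria does not list this reason. Such a participant may have a real week-12 value. The example works only if these cases are handled as withdrawals, which is not stated.

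**Conclusion.** The point holds as a stated analysis choice that does not fit the endpoint. It is not a detail left for an analysis plan to supply. Carrying forward can credit a participant with week-12 success on the strength of an earlier value, and no stated analysis tests that assumption.

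A reader might go further and conclude that the rule necessarily inflates the KYCT effect. The article does not support that. The supported statement is that the rule can favour KYCT where the drug works on treatment, by an amount that depends on unknown dropout outcomes. At the planned 15% dropout, the scenarios shown differ from failure counting by 2.25 to 7.5 points, and one null scenario gives a type I error of about 8%. The size is moderate. The change should be made, but the trial does not fail without it.

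**What to change.** For the primary endpoint, replace the carry-forward rule as follows:
- A participant with no week-12 SUA is a non-responder.
- Withdrawn participants are asked to attend for SUA at week 12, and that value is used where they agree.
- One sensitivity analysis varies the missing-data assumption, by multiple imputation or a tipping-point analysis. Carrying forward is kept as a sensitivity analysis at most.

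For percent change in SUA, use a mixed model for repeated measures or multiple imputation instead of carrying forward. State how participants who stop the drug but stay in follow-up are scored.

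Study design says that recruitment ended in July 2023, so the change must be fixed and dated before unblinding, and best before the first of the two unblinding steps, when groups A and B are revealed. If that has passed, it should be labelled post hoc.

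The cost is analysis wording, the effort of obtaining week-12 samples from those who left, and possibly a somewhat smaller estimated difference. No patients are added. Power remains above the planned 0.80 with equal dropout of 15% or 20%, but falls to about 0.70 if dropout is 20% on KYCT and 10% on placebo. Retaining participants to week 12 therefore matters.

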#### Participant self-withdrawal

1) Participants who are unwilling or unable to continue with the clinical trial for any reason and request to withdraw from the trial are considered to have self-withdrawn;2) Participants who do not explicitly request to withdraw but do not receive treatment or participate in follow-up visits are considered lost to follow-up.

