### Ineligibility criteria

(1) Incorrectly enrolled subjects who did not meet all inclusion criteria or met any exclusion criteria; (2) Subjects who met inclusion criteria but did not take the study medication or have no follow-up data; (3) Subjects who switched medications or added unspecified co-medications, especially those that could significantly impact assessment of efficacy and safety.

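### Efficacy set: the ineligibility rules remove subjects for medication changes made after randomisation, and separately contradict the last-observation rule for subjects with baseline data only

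*Protocol article*

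**What the plan says.** Four statements in the protocol article bear on who is counted for efficacy.

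- **Data analysis, analysis sets.** "The complete analysis set (FAS) and per protocol set (PPS) were used for efficacy evaluation analysis". Neither set is defined further.
- **Data analysis, excluded cases.** "Excluded cases were not included in the efficacy statistical analysis". The same sentence keeps those who were treated and have a safety record in the adverse reaction analysis. That is the only analysis in which the article keeps them.
- **Data analysis, dropouts.** "Dropouts with baseline data were included in efficacy analyses using the last observation carried forward".
- **Ineligibility criteria.** Criterion 3 lists "Subjects who switched medications or added unspecified co-medications, especially those that could significantly impact assessment of efficacy and safety". Criterion 2 lists "Subjects who met inclusion criteria but did not take the study medication or have no follow-up data".

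Under Participant self-withdrawal, the article adds: "Participants who do not explicitly request to withdraw but do not receive treatment or participate in follow-up visits are considered lost to follow-up". The section Handling of dropout cases covers both early withdrawal and loss to follow-up.

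**The concern.** There are two separate problems, each arising from a different criterion.

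**Medication changes (criterion 3).** Switching or adding a medicine happens after randomisation. It can be prompted by a poor response, and so can differ between arms even under blinding. Removing such subjects from the PPS is ordinary practice. Removing them from all efficacy analysis means that the FAS no longer compares the groups as allocated. It also treats similar patients differently: one who does badly and withdraws stays in by last observation carried forward, while one who does badly and adds a medicine disappears.

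**No follow-up data (criterion 2).** A randomised subject with a baseline value and no later visit is removed by this criterion and included by the dropout rule. The primary denominator is then contradictory, and the choice could be made after the data are seen.

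**Working it through.** The plan gives no figure on this point, so there is none to reproduce.

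**Inputs**

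- Response rates of 60% (KYCT) and 30% (control): Sample size calculation.
- 63 per arm: same section. The dropout step checks: 53/(1 − 0.15) = 62.4, rounded up to 63.
- Primary endpoint, SUA below 420 µmol/L at week 12: Primary efficacy endpoint.
- Entry SUA above 480 µmol/L: Inclusion criteria, item 3.
- Shares removed or without follow-up: the article gives none. Those below are assumptions.

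**Step 1. Who the excluded cases are.** The article does not say that they are the subjects in Ineligibility criteria. Three things point there. Some of them received treatment, so they are not only screening failures. Data analysis treats them apart from dropouts. Ineligibility criteria is the only other subject-level category that applies after enrolment.

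**Step 2. Effect of criterion 3 at the planned rates.** Let p be an arm's true rate and f the share removed. If all those removed are non-responders, the observed rate is p/(1 − f). If all are responders, it is (p − f)/(1 − f). With f = 0.10:

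- Non-responders: 0.60/0.90 = 66.7%; 0.30/0.90 = 33.3%.
- Responders: 0.50/0.90 = 55.6%; 0.20/0.90 = 22.2%.

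| 10% removed from | All non-responders | All responders |
|---|---|---|
| Control only | 60.0 − 33.3 = 26.7 points | 60.0 − 22.2 = 37.8 points |
| Both arms | 66.7 − 33.3 = 33.3 points | 55.6 − 22.2 = 33.3 points |
| KYCT only | 66.7 − 30.0 = 36.7 points | 55.6 − 30.0 = 25.6 points |

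The true difference is 30 points throughout. Differences are taken before rounding.

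**Step 3. Effect of criterion 3 with no true effect.** Take 30% in both arms, with 5% of the KYCT arm and 15% of control removed. That leaves 63 × 0.95 = 59.85 and 63 × 0.85 = 53.55 subjects. The rejection probability is a normal approximation for the two-sided 5% test, with the pooled standard error in the critical value.

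- All responders: 0.25/0.95 = 26.3% and 0.15/0.85 = 17.6%. The spurious difference is +8.7 points, and rejection is about 19.5%.
- All non-responders: 0.30/0.95 = 31.6% and 0.30/0.85 = 35.3%. The spurious difference is −3.7 points, and rejection is about 7.1%.
- Equal shares of the same kind removed from both arms: no spurious difference.

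**Step 4. Criterion 2 against the dropout rule.** A carried-forward baseline above 480 µmol/L is always a non-response. Suppose 5 of 63 subjects in one arm have baseline only and 35 respond:

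- Criterion 2 followed: 35/58 = 60.3%.
- Dropout rule followed: 35/63 = 55.6%.

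If the same share d of both arms has baseline only, and the rates are 60% and 30% among the rest:

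| d | Removed: rates, power | Carried forward: rates, power |
|---|---|---|
| 5% | 60% vs 30%, 92.0% | 57.0% vs 28.5%, 90.8% |
| 10% | 60% vs 30%, 90.5% | 54.0% vs 27.0%, 87.9% |
| 15% | 60% vs 30%, 88.8% | 51.0% vs 25.5%, 84.6% |

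The same data thus give two different primary results, although power stays above 80% either way.

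**The case against.** The strongest reply is that the article never equates excluded with ineligible, never says outright that the FAS loses these subjects, and may leave the definitions of both sets to the full protocol or analysis plan. It is right that the link is inferred. But the article does state a rule, applies it to efficacy analysis as a whole, and makes clear that treated subjects can fall under it. The point concerns that stated rule, not a missing definition.

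A second reply is that arm-dependent switching may be rare. Follow-up is 12 weeks, the trial is double-blind and the subjects are asymptomatic. Criterion 3 does not mention urate-lowering products, and etoricoxib for gout attacks is supplied under the protocol, so it is arguably not an unspecified co-medication. This limits the likely size of the bias but does not remove it, and the article gives no frequency.

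A third reply is that the baseline-only conflict has a modest effect. That stands when the arms lose similar shares, as Step 4 shows.

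A reader might infer that dropping medication changers inflates the apparent benefit of KYCT. The documents do not support a direction. Someone who adds an effective product may be below 420 µmol/L at week 12, and removing that person lowers the arm's rate. Removing failures mainly from control would work against KYCT. A reader might also infer that the rule on medication changes contradicts the dropout rule. It does not: only criterion 2 does.

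**Conclusion.** Both points hold. Read naturally, the plan removes subjects from the FAS for a medication change after randomisation. The resulting bias is of unknown direction. In the illustrations it moves a true 30-point difference to between 25.6 and 37.8 points, and under no effect it raises the rejection rate to between about 7% and 20%. These sizes rest on assumed removal shares of 5% to 15% and on those removed being all responders or all non-responders. They show what the rule permits and are not a forecast.

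Separately, the plan both removes and counts subjects with baseline data only. In the example this changes one arm's rate by just under 5 points. This conflict is in the text itself and needs no assumption about switching, although its size depends on how many such subjects there are.

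**What to change.** - Apply ineligibility criterion 3 to the PPS only. Keep these subjects in the FAS in their randomised arm.
- Fix one primary-endpoint rule for them before unblinding. One option is to count non-response after another urate-lowering product is started, with observed week-12 values as a sensitivity analysis. The reverse order is also defensible; what matters is that the choice is made in advance.
- Reconcile criterion 2 with Data analysis. Keep treated subjects with baseline data only in the FAS, where the carried-forward baseline already counts as non-response. In the FAS, limit criterion 2 to subjects who took no study medication, and have the dropout rule say the same, because the definition of loss to follow-up also covers people who receive no treatment.
- State that excluded cases means the subjects in Ineligibility criteria, and say for each criterion which analysis set it affects.

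The cost is wording only, with no change to data collection or patient management. Observed success rates may be slightly lower.

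### The declared primary analysis (ANCOVA, outcome not named) does not match the binary primary endpoint on which the trial was sized, so the primary effect measure is undefined

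*Protocol article*

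**What the plan says.** The protocol article describes the primary endpoint and its analysis in four places.

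- **Primary efficacy endpoint:** "The proportion of participants who maintained SUA levels <420 umol/L at week 12". This is a yes/no outcome per participant. The abstract also gives a proportion below 420 umol/L.
- **Sample size calculation:** the trial is sized by a two-proportion formula at 60% v 30%, two-sided 0.05, power 0.80. This gives 53 per group, and 63 per group (126 in total) after 15% dropout.
- **Data analysis, on lifestyle confounding:** "our primary analysis will employ analysis of covariance (ANCOVA) adjusting for key lifestyle covariates", namely "including physical activity levels (measured in MET-minutes/week) and daily purine intake (quantified through 24-hour dietary recalls"). The outcome of this model is not stated. The next paragraph says that "stratified randomization by baseline sUA tertiles (7.0-7.5, 7.6-8.5, >8.5 mg/dL) and sex ensures balanced subgroup distributions".
- **Data analysis, general tests:** for normally distributed data, "We used an independent sample t-test to compare differences between the two groups"; for skewed data, "We used the Mann-Whitney test to compare differences between the two groups". Paired t, Wilcoxon and Spearman complete the list. A binary-outcome method appears once: "The proportion of participants attaining the MCID (≥1.2 mg/dL sUA reduction) will be compared between treatment arms using logistic regression", adjusted for baseline sUA, sex and baseline sUA tertiles. The article classes that endpoint as exploratory.

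**The concern.** ANCOVA is ordinarily a model for a continuous outcome. Declared as the primary analysis of a responder endpoint, with no outcome named, it leaves open what the trial's main result will be. If the outcome is mean SUA or percent change, the primary analysis does not estimate the quantity on which the trial was sized. If it is the 0/1 response, the analysis is a linear probability model and its arm coefficient is a risk difference. A reader could also argue for the adjusted logistic model given for the MCID endpoint. These analyses can disagree, and each could claim some support in the text.

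Timing makes this matter. Under Random allocation and blinding, groups A and B are revealed before the statistical analysis, and only the identity of the arms is held back until it is finished. The choice of primary model has to be fixed before that first step.

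Randomisation is also stratified by baseline sUA and sex, and the exploratory model adjusts for both. Neither is named for the primary model, although baseline SUA can be expected to predict who falls below 420 umol/L.

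**Working it through.** **1. The plan's own figure.** Inputs from Sample size calculation: p1 = 0.60, p2 = 0.30, two-sided 0.05, power 0.80, dropout 15%.

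Unpooled formula: n = [p1(1−p1) + p2(1−p2)] × (z_α/2 + z_β)² / (p1−p2)² = (0.24 + 0.21) × (1.960 + 0.842)² / 0.09 = 39.2, so 40 per group. Other two-sided variants at power 0.80 give 42 (Fleiss), 42 (arcsine), 44 (pooled) and 49 (Fleiss with continuity correction). None gives 53. The unpooled formula at power 0.90 gives 0.45 × (1.960 + 1.282)² / 0.09 = 52.5, so 53. The dropout step reproduces: 53 / 0.85 = 62.4, so 63 per group and 126 in total.

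At 53 per group, power for 60% v 30% is 0.885 (normal approximation), 0.878 (exact, chi-square test) or 0.836 (Fisher). The stated power and the 53 need reconciling, but the present point does not depend on that. What matters here is that the calculation is for a difference in proportions.

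**2. Endpoint and analysis side by side.**

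| Endpoint | Type | Analysis stated |
|---|---|---|
| Primary: SUA <420 umol/L at week 12 | Binary | ANCOVA with lifestyle covariates, outcome not named |
| Exploratory: MCID attained | Binary | Logistic regression on arm, baseline sUA, sex, sUA tertiles |
| Quantitative data in general | Continuous | t-test or Mann-Whitney between arms; paired t or Wilcoxon within arms |

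The exploratory responder endpoint has a matched model and the primary one does not. The Discussion cites a different primary threshold (below 6 mg/dL), but that too is a responder endpoint, so the mismatch remains either way.

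**3. What if ANCOVA is run on the 0/1 outcome?** Simulation with 53 per arm, 1000 trials per setting, one covariate unrelated to outcome, and an assumed latent correlation between baseline and week-12 SUA. The no-effect setting has 30% in both arms.

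| Assumed correlation | Linear, no baseline | Logistic, no baseline | Linear, with baseline | Logistic, with baseline |
|---|---|---|---|---|
| 0 | 0.871 | 0.871 | 0.872 | 0.873 |
| 0.3 | 0.884 | 0.884 | 0.907 | 0.909 |
| 0.5 | 0.872 | 0.872 | 0.927 | 0.928 |
| 0.7 | 0.891 | 0.891 | 0.960 | 0.961 |

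Entries are power at 60% v 30%. Linear and logistic power differ by at most 0.002. Type I error is 0.045 to 0.063 across all models (Monte Carlo standard error √(0.05 × 0.95 / 1000) = 0.007). A separate run of 4000 trials of the linear model gave a mean estimated risk difference of 0.301 against a true 0.30, power 0.877, and type I error 0.059 with both arms at 40%.

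**4. What does naming baseline SUA gain?** From the table, for logistic regression: 0.909 − 0.884 = 0.025 at correlation 0.3; 0.928 − 0.872 = 0.056 at 0.5; 0.961 − 0.891 = 0.070 at 0.7. A second simulation cut the baseline off at the entry criterion (above 480 umol/L, assumed residual SD 70). Adjusted power was 0.903, 0.920 and 0.946 at correlations 0.3, 0.5 and 0.6, against 0.890 to 0.899 unadjusted. The gain is thus roughly 0.01 at 0.3, 0.02 to 0.03 at 0.5 and 0.05 at 0.6. The documents give no correlation, so all of these are conditional on assumed values.

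**The case against.** The strongest defence is that the article condenses a fuller protocol, and that a statistical analysis plan would normally supply the test of proportions and the full covariate list. That stands for the missing mention of a chi-square or Fisher test, which is no finding by itself. It does not answer the main point: the article does state a primary analysis, and a later plan would have to override or reinterpret that sentence to fit the endpoint.

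Several stronger readings are tempting, and the documents do not support them.

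- *ANCOVA on a yes/no outcome is invalid or misses the powered effect.* The linear model's arm coefficient is a risk difference, type I error is near nominal, and power matches logistic regression.
- *Baseline SUA is excluded from the primary model.* The covariates are introduced by the word *including*, so the list is not exhaustive. Baseline SUA and sex are unnamed, not ruled out.
- *The document has no method for a proportion.* It has one, assigned to the exploratory endpoint only.
- *Efficacy will be judged on within-arm change.* Before/after tests are listed, and entry above 480 umol/L makes some regression to the mean likely in both arms. But between-group tests are listed alongside, the stated hypothesis is against placebo, and nothing rests efficacy on a within-arm test. Any figure for the size of that fall would depend on an assumed population mean and SDs.
- *The percent-change secondaries are assigned unadjusted t-tests.* The test list is generic, and the ANCOVA may have been meant for these outcomes.
- *The trial is short of power without adjustment.* At 53 per group unadjusted power is about 0.88, above the planned 0.80.
- *Centre must be in the model.* It is not a stated stratification factor.

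**Conclusion.** The point holds as a mismatch in stated text. A binary endpoint and a two-proportion sample size are paired with a primary ANCOVA whose outcome is not named, while the fitting binary-outcome model is given only to an exploratory endpoint. It follows that the primary effect measure is undefined and that the stratification factors are not named in the primary model.

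The consequence is mainly one of definition and analytic freedom. If the ANCOVA is on mean or percent-change SUA, the main result will not address the powered endpoint. If it is on the 0/1 response, little is lost numerically. Leaving out baseline SUA would cost roughly 0.01 to 0.05 in power at assumed correlations of 0.3 to 0.6 with the baseline cut off at entry, and slightly more in the simulation without the cut-off. The textual finding needs no assumption; the precision figures rest on the assumed correlations and on 60% v 30%.

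**What to change.** In Data analysis, replace the sentence that makes ANCOVA with lifestyle covariates the primary analysis:

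- **Primary:** logistic regression of SUA <420 umol/L at week 12 (yes/no) on arm, continuous baseline SUA and sex, reporting the standardised risk difference with 95% CI.
- **Continuous SUA outcomes:** ANCOVA with baseline SUA as a covariate, restricted to these outcomes.
- **Within-arm before/after tests:** descriptive only.

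The cost is wording and a small amount of programming. Baseline SUA and sex are already used for stratification, so no new data are needed and the sample size is unaffected.

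The one real cost is documentation. Study design says recruitment ended in July 2023, and the blinding and analysis sections are partly in the past tense, so the article does not show whether unblinding has taken place. Record that the change was made before the first unblinding step. If it was not, label the new analysis as post hoc.
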